### 7.2. Statistical Methods for Additional Analyses

We will fit multilevel multiple mediation models in Mplus 6 [72], entering all hypothesized mediators simultaneously [73]. The conceptual model of mediation is depicted in Figure 1. 

We will calculate the intervention effect for each mediator, the effect of each mediator on the outcome (suicidal ideation), and the intervention effect that was mediated by each mediator. For each model, we will compute the total indirect effects of the intervention (i.e., the total effect of intervention mediated by the sum of the mediating factors) and the single indirect effect for each mediator as suggested by Preacher and Hayes [73]. Moreover, we will calculate the program’s direct effect (i.e., the effect not explained by the hypothesized mediators). The randomization occurred at the school level; therefore, we will enter school as the second level and individuals as the first level. To control for variability across schools, we will use the stratification option in Mplus. 

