### 1.2. Objectives

The main objective of this study is to develop a blended intervention to reduce suicidal ideation and to test its effectiveness among adolescents in secondary schools in Chile at post-intervention and 3-month, 6-month, and 12-month follow-up. Additionally, the study will identify and compare changes in depressive and anxiety symptoms, hopelessness, emotional regulation, and problem-solving skills among adolescents in the intervention group schools and the control group. Finally, we will explore the influence of potential mediators on the observed effects of the integrated blended intervention. 

We hypothesize that the intervention would reduce suicidal ideation among the treatment group compared to the control group at post-intervention. Specifically, we hypothesize that the intervention will lead to the following changes among the treatment group compared to the control group at post-intervention and follow-up: reduced feelings of depression, anxiety, and hopelessness, increased emotional regulation, and problem-solving skills. Finally, we hypothesize that the effect of the integrated blended intervention on suicidal ideation will be mediated by hopelessness, emotional regulation, and problem-solving skills, and partially mediated by CBT skills acquired from the intervention. The results of this study will provide relevant insights to reinforce direct and indicated interventions in educational settings. 

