### 2.1. Study Setting

Participants will be adolescents attending schools with secondary education (grades 9–11), mixed sex, located in three different cities in the South of Chile, with at least two classes per year. We expect to recruit at least ten schools per arm. Each arm should include 140 eligible students.

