### 3.8. Sample Size

This sample size considers a loss at follow-up of 20% of the students. Considering a 20% of school rejection at the recruitment stage, we expect to recruit 12 schools. Studies of similar school-based interventions report effect sizes of at least 0.4 standard deviation using symptoms questionnaires as proposed here [71]. We used the results previously observed by Hetrick et al. [49] and the clustersampsi command in Stata Software to estimate the number of clusters in two arms, using the following command: clustersampsi, samplesize mu1(X1) mu2(X2) sd1(Y1) sd2(Y27) m(Z) rho(R). Where X1 = mean in arm 1; X2 = mean in arm 2; Y1 = standard deviation (SD) in arm 1; Y2 = SD in arm 2; Z = number of children per school on average (harmonic mean) (*n* = 14); and R = intracluster correlation. The two arms will be balanced for school size. 

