## 4. Assignment of Interventions: Allocation

Randomization will be performed once all schools are recruited. Schools will be randomly assigned to either group with a 1:1 allocation as per computer-generated randomization. In order to reduce the risk of allocation bias, the size of the schools and the vulnerability index will be taken into account to balance the groups. 

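### The mediation model enters school as level 2 and then appears to use it as a stratum too, which a school-randomised comparison cannot support

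*Protocol article*

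**What the plan says.** Section 7.2 plans multilevel multiple mediation models in Mplus. It gives randomisation by school as the reason for a two-level structure: "therefore, we will enter school as the second level and individuals as the first level". The next sentence adds a further device and states its purpose: "To control for variability across schools, we will use the stratification option in Mplus". No stratification variable is named, and neither sentence mentions any unit other than school and individual.

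Section 4 fixes the unit of allocation: "Schools will be randomly assigned to either group with a 1:1 allocation as per computer-generated randomization". It adds that school size and a vulnerability index will be considered in balancing the arms, but it does not say that strata are formed from them. Section 4.1 repeats the 1:1 allocation without strata.

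Section 1.2 makes mediation a stated hypothesis: the effect on suicidal ideation is expected to be "mediated by hopelessness, emotional regulation, and problem-solving skills, and partially mediated by CBT skills acquired from the intervention".

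**The concern.** Clustering and stratification do opposite things to a standard error. Declaring school as a cluster, or as level 2, keeps the variation between schools in the standard error of any effect that is compared between schools. Declaring school as a stratum takes that variation out, because differences between strata are treated as fixed and known.

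In this trial the arm-to-mediator path and the direct effect of arm are purely between-school comparisons. Variation between schools is the yardstick for them and cannot be controlled away. If the second sentence is carried out as it reads, it either cancels the protection given by the first or produces a model whose variance cannot be computed. At stake are the conclusions about mechanism: standard errors that are too small on the arm-to-mediator paths would make it too easy to report that the intervention shifts a mediator.

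**Working it through.** **Inputs**

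- Arm is constant within school (Section 4, randomisation of schools 1:1).
- Average students per school: m = 14 (Section 3.8).
- Schools: at least ten per arm, so J = 20 (Section 2.1). This agrees with the 140 students per arm given there, since 10 × 14 = 140. Section 3.8 gives 12 without saying whether that is a total or per arm. The variance ratio below does not depend on J.
- Intracluster correlation (ICC): Section 3.8 has only the symbol R. Values of 0.02, 0.05 and 0.10 are assumed.
- The article states no figure for the precision of the mediation model, so there is none to reproduce.

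**Reading A: school is the stratum and is not treated as a cluster**

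Scale the mediator's total variance to 1, with ICC between schools and 1 − ICC within schools. For the difference between arms in the mediator mean, with J/2 schools per arm:

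- True variance = (4/J) × [ICC + (1 − ICC)/m]
- Variance reported with school as stratum = (4/J) × (1 − ICC)/m
- Ratio = 1 + m × ICC/(1 − ICC)
- Actual two-sided error of a nominal 5% test = 2 × [1 − Φ(1.96/√ratio)]

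| Assumed ICC | Ratio at m = 14 | Reported SE as a share of the true SE (1/√ratio) | Actual error |
|---|---|---|---|
| 0.02 | 1 + 14 × 0.02/0.98 = 1.29 | 0.88 | 8.4% |
| 0.05 | 1 + 14 × 0.05/0.95 = 1.74 | 0.76 | 13.7% |
| 0.10 | 1 + 14 × 0.10/0.90 = 2.56 | 0.63 | 22.0% |

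A simulation of the arm-to-mediator path (10,000 replicates per setting, 14 students per school, 12, 20 or 24 schools) gave 8.2% to 9.0%, 13.5% to 13.9% and 21.7% to 22.4% at the same three ICCs. The number of schools made little difference.

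After the planned 20% loss of students, m = 14 × 0.8 = 11.2. The formula then gives about 7.7%, 12.0% and 19.1%.

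**Reading B: school is both cluster and stratum**

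Variance between clusters within a stratum needs at least two clusters in that stratum. Here each stratum holds one, leaving 1 − 1 = 0 degrees of freedom per stratum and 20 − 20 = 0 overall. The variance is not estimable.

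**Reading C: school is the cluster and the stratum is a blocking factor**

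If strata are formed from school size or the vulnerability index and each contains several schools per arm, between-school variance stays in the standard error. With two strata, for example, 20 − 2 = 18 degrees of freedom remain. This reading is sound, but Section 7.2 does not state it.

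**Check of the cluster-only form**

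In the same simulation, school means were compared between arms with a t reference on J − 2 degrees of freedom. The error rate was 4.6% to 5.3% over 12, 20 and 24 schools and ICCs from 0.01 to 0.10.

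**The case against.** The strongest reply is that the stratum is never named. Section 4 mentions two school-level factors used to balance the arms, and strata built on either would do no harm. That stands, and it makes the finding conditional. It does not rescue the sentence: Section 7.2 gives variability across schools as the purpose and names no blocking factor, and Sections 4 and 4.1 define no strata.

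A second reply is that the 8% to 22% figures describe a model without clustering, whereas the preceding sentence does enter school as level 2. That also stands. The figures show what Reading A would cost; they do not predict what the analyst will run. With both options applied to school, the likelier result is a model that fails visibly. The rates also concern the arm-to-mediator path only. A claim of mediation needs a mediator-to-outcome path as well, and no error rate for the indirect effect has been derived.

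A reader might also infer that there are too few schools for a model "entering all hypothesized mediators simultaneously". The documents do not support that as an error. Entering mediators together is legitimate. The article does not say which paths are estimated between schools, its conceptual figure is not shown, and that detail commonly sits in a fuller analysis plan. The number of schools is itself unsettled: Section 2.1 says "We expect to recruit at least ten schools per arm" and Section 3.8 says "we expect to recruit 12 schools". A small number of schools makes standard errors fragile, but small-sample methods exist for that.

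**Conclusion.** The point holds in conditional form. On the natural reading, with school as the stratum, the two consecutive statements in Section 7.2 cannot both be carried out in a usable way. Either between-school variance is lost, with the test of an arm-to-mediator path running at about 8%, 14% or 22% instead of 5% (assumed ICCs of 0.02, 0.05 and 0.10, 14 students per school), or the variance is not estimable. This is a procedure and a purpose stated wrongly, not a detail left for later.

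Two stronger conclusions are tempting but not supported. One is that the mediation standard errors will necessarily be wrong: they will not be if the stratum turns out to be a proper blocking factor. The other is that the trial's main result is at risk: Section 7.1 fits the outcome models with school as a random factor, and the defect lies in an exploratory analysis listed under additional analyses.

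**What to change.** Delete the stratification sentence from Section 7.2 and keep school only as the cluster, that is, as level 2.

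If stratification is to stay, name the variable. It should be a school-level blocking factor actually used in the randomisation, such as school size or the vulnerability index, and each of its strata should contain several schools in each arm. Section 4 would then need to say that allocation was stratified on that factor.

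This is a change of wording that can be made before analysis and needs no new data. The cost is wider intervals for the arm-to-mediator paths and the direct effect than school-as-stratum would give. Those wider intervals are the valid ones.

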### 7.3. Interim Analyses

There will not be interim analyses because the data will be analyzed at the end of the trial.

### 7.4. Methods in Analysis to Handle Protocol Non-Adherence and Any Statistical Methods to Handle Missing Data

The primary outcome will be assessed using an intention-to-treat analysis. Missing data will be reduced to a minimum by using the appropriate measures; encouraging students to fill out the whole questionnaire, a research assistant will revise the questionnaire when students end the evaluation and ask to complete the instruments if some questions are unanswered. Multiple imputations will be used to handle missing data in the primary and secondary analyses.

### 7.5. Plans to Give Access to the Full Protocol, Participant Level-Data, and Statistical Code

The data set produced during the study will be available in an international database repository (UK Data Service).

## 8. Oversight and Monitoring

### 8.1. Composition of the Coordinating Center and Trial Steering Committee

Daily support for the trial will be provided by the principal investigator, who takes supervision of the trial. Additionally, there is a data manager who organizes data collection and assures data quality. The study coordinator helps in trial registration and will coordinate study visits and reports. Study research assistants will help to identify potential participating schools, collect informed consents, ensure follow-up according to protocol, and resolve doubts from school staff or participants. 

The study team will meet weekly during the whole duration of the study. There is no trial steering committee or stakeholder and public involvement group. The Ethical Scientific Committee of the Universidad de Talca will check the presence and completeness of the investigation.

### 8.2. Composition of the Data Monitoring Committee, Its Role, and Reporting Structure

A monitor from the Ethical Scientific Committee of the Universidad de Talca will check once a year the presence and completeness of the investigation. This committee is independent of the sponsor and has no competing interests; further details about its charter can be asked via email: [contact].

### 8.3. Adverse Event Reporting and Harms

The intervention does not infer harm among the participants. However, any situation that compromises the physical and psychological integrity of participants occurring during the intervention process will be reported by the psychologist working with the students by filling out a predesign form. This professional will activate the protocol for managing suicidal behavior in schools already in place in all educational institutions in Chile (MINSAL, 2019). This protocol includes contacting school authorities, main caregivers, and local health providers in order to obtain a quick response from health services. It also includes a follow-up and case management. In parallel, the psychologist will inform the principal investigator and the project coordinator, who will support the whole process. To reduce the risk of low implementation of this protocol, we will train the school personnel before the intervention. 

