## 3. Interventions

### 3.1. Explanation for the Choice of Comparators

All participants in the intervention group will be sent to primary care centers, where a protocol for managing suicidal ideation defined by the Chilean Ministry of Health will be applied [62]. The whole procedure will be described as Treatment-As-Usual (TAU). TAU consists of identification and assisted referral to a primary care clinic, where trained psychologists will assess the symptomatology and propose a course of actions, from initiation of psychotherapy to referral to a general practitioner to initiate medication if needed. Psychotherapy in primary care clinics consists of a range of 4–8 sessions twice a month. Most of the content of the psychotherapy is based on the Cognitive-Behavioral Model. When needed, general practitioners may suggest using medications, which generally are SSRI antidepressants (e.g., Fluoxetine, Sertraline). A medical check-up is conducted every month or every two months.

The control group will receive the Treatment-As-Usual (TAU). In order to reduce the risk of performance bias, all adolescents who need to have care in a public health center will receive the same treatment. The public health centers have similar structures and resources, they have standardized protocols for managing mental disorders and suicide risk and the professionals have similar backgrounds and skills. To test potential biases, we will register and quantify all different interventions delivered by health centers.

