### 3.2. Intervention Description

#### 3.2.1. Experimental Intervention

##### Internet-Based Component (Reframe-IT)

It has been described elsewhere [46,48]; it comprises eight modules of CBT delivered over a 10-week intervention period. The program will be administered at schools by trained school psychologists (one psychologist per school). The authors will deliver the training of the program. Each participant will have access to their personalized web page accessed via secure login. Each module will be completed in the psychologist’s presence and participants will also be able to access it at home 24 h a day. For safety reasons, the program does not have social networking functions. Standard CBT approaches are delivered in the intervention, focusing on SI and behaviors. The modules and their respective topics are: -Module 1: engagement and problem identification;-Module 2: emotional recognition and distress tolerance;-Module 3: identification of automatic negative thinking;-Module 4: behavioral activation help seeking;-Module 5: behavioral activation activity scheduling (including relaxation techniques);-Module 6: problem solving;-Module 7: cognitive restructuring;-Module 8: wrap-up session.

These contents are delivered via a series of video diaries by young people as main characters with an adult ‘host’ character highlighting the CBT contents presented in the context of the video diaries. There are two activities per module. Overall, each module lasts about 25 min. The site has a message board through which the participant could communicate with research therapists (clinical psychologists), who also check completed activities and respond with personalized but standardized messages. Finally, a series of fact sheets cover various related topics including managing SI, plus downloadable relaxation MP3s.

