### 3.5. Provisions for Post-Trial Care

There is no potential harm or damage in this trial. The intervention group will receive an evidence-based intervention and the control group will receive the usual care in health centers.

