### 3.6. Outcomes

Self-report questionnaires assessing primary and secondary outcomes will be administered at baseline (one week before the start of the intervention), at post-intervention, and follow-up (3, 6 and 12 months). Primary and secondary outcomes will be measured electronically using Qualtrics.

Participants will be asked sociodemographic information including, age, sex at birth, gender, race/ethnicity, education, family income, and psychological/psychiatric treatment.

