#### 3.6.2. Secondary Outcomes and Questionnaires

Suicide attempt: two questions assessing whether participants had attempted suicide; if yes, how many attempts?

Anxiety as trait and as state: The State–Trait Anxiety Inventory (STAI-X) [65] is a self-report questionnaire with two scales of 20 items, each assessing state and trait levels of anxiety. Respondents indicate how they generally feel on a 4-point Likert scale from 0 (almost never) to 3 (almost always). The minimum score is 0 and the maximum score is 60 for both scales. Higher scores mean higher trait or state anxiety levels. It has been validated in the Chilean population aged 13–60 years old [66].

Hopelessness: The Beck Hopelessness Scale [67] is a self-report scale with 20 true or false items, nine of which are keyed ‘false’ and 11 are keyed ‘true’. For every statement, each response is assigned a score of 0 or 1 and the total hopelessness score is the sum of the scores on the individual items. The minimum score is 0 and the maximum score is 20. A higher score means higher hopelessness levels.

Social problem solving: The short form of the Social Problem-Solving Inventory Revised (SPSI-R Short Form) [68] is a 25-item self-report instrument measuring two adaptive problem-solving dimensions (positive problem orientation and rational problem solving) and three dysfunctional dimensions (negative problem orientation, impulsivity/carelessness style, and avoidance style). Each item is rated on a 5-point scale ranging from ‘not at all true of me’ (0) to ‘extremely true of me’ (4). The minimum score is 0 and the maximum score is 75. A higher score means a higher social problem-solving capability.

Cognitive-behavioral skills: The Cognitive-Behavioral Therapy Skills Questionnaire (CBTS) [69] is a 16-item scale with two scales measuring two skills: cognitive restructuring (CR) and behavioral activation (BA). Respondents rank each item on a 5-point Likert scale from 1 (I don’t do this) to 5 (I always do this). The minimum score is 15 and the maximum score is 80. A higher score means a higher presence of cognitive-behavioral skills. To assess general CBT skills, we have removed those items that refer exclusively to the practice of CBT sessions (e.g., keep track of the signs and symptoms of my condition); therefore, general CBT skills could be assessed before and after the intervention in both groups. 

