## 7. Statistical Methods

### 7.1. Statistical Methods for Primary and Secondary Outcomes

We will use descriptive statistics to assess balance across arms at baseline. The primary between-group analysis will be carried out on an intention-to-treat basis for 3-month SIQ scores. We will use linear mixed effects model analysis to compare the intervention and control groups regarding the change in outcome measures from baseline to post-intervention and the follow-up time point. The school is included as a random factor for each outcome measure to account for possible school effect. We will use Fisher’s exact test to compare the frequency of suicide attempt cases between groups. We also will conduct a Complier Average Causal Effect (CACE) analysis to assess the impact of the number of sessions on the primary outcome. All analyses will be performed using STATA 15.01. 

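### Adverse-event form reporting is tied to the programme psychologist and the intervention period, so harms other than self-reported suicide attempts and questionnaire outcomes cannot be compared between arms or seen during follow-up

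*Protocol article*

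**What the plan says.** Section 8.3 (Adverse Event Reporting and Harms) sets one route. Situations that compromise a participant's integrity "occurring during the intervention process will be reported by the psychologist working with the students", using a predesigned form. The same person activates the schools' suicidal-behaviour protocol and informs the principal investigator and the project coordinator.

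The description of the internet-based component says who this person is: "The program will be administered at schools by trained school psychologists (one psychologist per school"). The same paragraph gives the duration: "it comprises eight modules of CBT delivered over a 10-week intervention period".

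For the comparator, Section 3.1 says "The control group will receive the Treatment-As-Usual (TAU"), delivered through primary care. No adverse-event reporter or form is named there. Section 3.6.2 has a research assistant log appointments and attendance at the clinics, which is a record of care received and not of events.

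Separately, Section 3.6.2 lists an outcome that is also a harm: "Suicide attempt: two questions assessing whether participants had attempted suicide; if yes, how many attempts". Section 3.6 has the self-report questionnaires "administered at baseline (one week before the start of the intervention), at post-intervention, and follow-up (3, 6 and 12 months"), and Section 7.1 plans Fisher's "exact test to compare the frequency of suicide attempt cases between groups".

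On the premise about harm, Section 3.5 states "There is no potential harm or damage in this trial", and Section 8.3 opens with a similar assurance about the intervention.

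**The concern.** The harms procedure fixes a reporter and a window that exist only in the intervention arm and only while the programme runs. Followed as written, it finds events by different means in the two arms and stops before follow-up begins.

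The trial enrols adolescents with a C-SSRS score of 3 or more and counts suicide attempts as an outcome, so harm is something for the trial to measure. Stating its absence as a premise, beside a one-sided reporting route, leaves the statement untested for every event that the questionnaires do not ask about.

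**Working it through.** There is no design figure to reproduce. The check sets the sections side by side and works out how much of a student's time in the trial the form covers.

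**Coverage by the stated duration**
- Intervention period: 10 weeks (Section 3.2.1).
- Follow-up: 12 months, taken as 52 weeks and assumed to run from the end of the intervention (Section 3.6).
- Share covered = 10 / (10 + 52) = 10 / 62 = 16%.

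**Coverage by Table 1**
- Blended intervention: June to September 2023, 4 months.
- June 2023 to the 12-month assessment in September 2024: 7 months in 2023 plus 9 in 2024 = 16 months.
- Share covered = 4 / 16 = 25%.

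Both figures are for intervention students. For control students the described coverage is 0%, since no reporter, form or window is given for them.

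**What each source can show**

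| Event | Control arm, during the intervention period | Either arm, after it |
|---|---|---|
| Suicide attempt, self-reported | Yes, at the post-intervention assessment | Yes, at 3, 6 and 12 months |
| Worsening ideation, anxiety, hopelessness | Yes, by questionnaire | Yes, by questionnaire |
| Death | No described route | No described route |
| Hospital admission | No described route | No described route |
| Non-suicidal self-harm as an event | No described route | No described route |
| Any event in a student who does not complete the assessment | No described route | No described route |

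**Size of the last row**
- Section 3.8 allows for 20% loss to follow-up, and Section 2.1 gives 140 eligible students per arm.
- If 140 is the number enrolled, 0.20 × 140 = 28 students per arm could have no self-report by the end.
- Section 3.3 adds that the data of intervention participants who leave are not analysed. An intervention student who deteriorates and withdraws would then drop out of the attempt comparison as well.

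**The case against.** The strongest reply is that the most relevant harm in this population is already covered. Attempts are asked about in both arms at every assessment and compared between groups. Ideation, anxiety and hopelessness are followed on the same schedule, and none of this depends on the psychologist. This stands. A reader might infer from Section 8.3 that harms cannot be compared at all or are invisible during follow-up; Sections 3.6, 3.6.2 and 7.1 do not support that.

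Two further inferences should be resisted.
- One is that a raw comparison of form counts would make the programme look harmful. Detection would indeed differ by arm, but no such comparison is planned. Section 8.3 describes a safety response and not an outcome dataset.
- The other is to count twelve supervised contacts (eight modules plus four sessions) against none. Control students have treatment-as-usual contacts in primary care, and research staff contact schools and participants during follow-up (Section 6.2). What the article lacks is a stated route from those contacts to the trial's event form.

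It can also be said that this is a condensed article, that Section 8.3 does not expressly exclude other reporters, that control schools may well have psychologists, and that the suicidal-behaviour protocol exists in all schools. All of that is fair, and it is why the point concerns the described route only. But the article does more than stay silent: it names a reporter and a window, and both belong to the intervention. The self-reports do not close the gap either, because they cannot record a death, do not ask about admissions, and are absent for students who leave.

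**Conclusion.** The point holds in a limited form. As described, event-form reporting is asymmetric between arms and covers roughly 16% to 25% of an intervention student's time in the trial. Self-reported attempts and the questionnaire outcomes are collected symmetrically to 12 months and remain comparable. Other harms, and events in students who withdraw or are lost, cannot be compared between arms or seen after the intervention.

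The no-harm statements are too absolute for a trial that measures suicide attempts as an outcome. The primary analysis is not affected. This is an inexpensive improvement to safety reporting.

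The conclusion assumes that the psychologist in Section 8.3 is the one who delivers the programme, and that the full protocol adds no separate route for control schools or follow-up. The percentages assume that the intervention lasts either the stated 10 weeks or the four calendar months in Table 1.

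**What to change.** Use the same predesigned form in both arms from baseline to 12 months. A named contact in each school would complete it when an event becomes known. Research staff outside the blinded outcome-evaluation team would check it at each scheduled assessment, so that the masking in Sections 4.2 and 5.1 is kept.

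Tabulate events by arm, recording how each one was detected, and present the table alongside the suicide-attempt comparison. Because programme sessions may still bring more events to light in one arm, the way of detection is needed to read the counts.

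Replace the no-harm statements in Sections 3.5 and 8.3 with one saying that harms will be recorded and reported by arm.

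The cost is some added reporting work for school contacts and research assistants. The form already exists, and contact with schools during follow-up is already planned (Sections 6.2 and 8.1). A contact in each control school would have to be named, since the article does not define one. The care response stays as documented.
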